| **Study Title:** | Improving Discharge Communication in the Emergency Department through Information Structuring: A Cluster Randomized Controlled Trial |
| **Short Title/Study ID:** | Improving Discharge Communication |
| **Protocol Version and Date:** | 02; 02/01/2015 |
| **Trial Registration:** | As soon as the ethics committee tells us to register. |
| **Study Category with Rationale:** | Clinical study, because the participants are patients with chest pain and patients with abdominal pain. The rationale for focusing on these target groups is twofold: First, chest pain and abdominal pain are common complaints, requiring efficient handling to maximize patient care while ensuring efficient use of resources. Second, patients with chest pain and patients with abdominal pain complaints often need additional work-up and follow-up (including treatment), which makes adequate discharge communication crucial. |
| **Clinical Phase:** | NA |
| **Background and Rationale:** | In an emergency department, effective discharge communication—i.e., information on diagnoses and instructions on further management at the time of discharge—represents a key step in medical care, with the potential to improve patient well-being and satisfaction, adherence to medication, and, ultimately, better health outcomes. Past research suggests that physicians’ communication is often not optimally structured and that patients fail to fully recall and understand the information received at discharge. In turn, psychological research suggests that information structuring can be a powerful tool to improve memory recall and understanding. Consequently, information structuring represents a tool to improve discharge communication and associated patient outcomes. |
| **Objective(s):** | The goal of the proposed study is to assess the potential of information structuring for improving discharge communication. Specifically, we aim to examine the advantages of an information-structuring skills training for physicians (compared to an emotion skills training) on discharge communication and associated patient outcomes, such as patients’ information recall and adherence to physician recommendations. We hypothesize that patients receiving structured discharge information from their trained physicians will be able to recall more information and show higher adherence to recommendations relative to controls (i.e., patients receiving discharge information from doctors trained in emotion-handling skills). |
| **Outcome:**  **Primary Outcome**  **Secondary Outcome** | Our primary outcome of interest is patients’ recall of the information provided during discharge consultations. In addition, a number of secondary outcomes associated with patient understanding of and adherence to physicians’ recommendations will be assessed. Recall performance is positively associated with comprehension^26^ and knowledge is a precondition for, albeit not synonymous with,^27^ compliance. Consequently, we hypothesize that recall performance will be positively correlated with patients’ understanding and adherence to physician’s recommendations.  Secondary outcomes:  -higher patient satisfaction  -more reliable medication intake  -more reasonable disease management |
| **Study Design:** | The study will use a cluster randomized controlled trial. Clusters of physicians (cohorts of six physicians commencing training in a three-month period; total of four clusters in the one-year intervention period) will be assigned to one of two types of training (information-structuring skills vs. emotion-handling skills). The primary outcome of the study will be patients’ recall of information as a function of physicians’ training. For this purpose, we aim to recruit 50 patients presenting to the emergency department with chest pain and 50 patients with abdominal pain in each three-month period (N = 400, in the one-year study period) and document the respective discharge communication (via audio recordings). In addition, each patient will be asked to recall the discharge information immediately after the discharge event, seven days and 30 days later, as well as complete a number of other measures to assess secondary outcomes, such as overall satisfaction and adherence to recommendations. The study will be conducted at the emergency department of the University Hospital of Basel (Switzerland). |
| **Inclusion/Exclusion Criteria:** | We will train a total of 24 physicians. The intervention will be assessed by interviewing a total of 400 patients who present to the emergency department of the University Hospital Basel with chest pain or with abdominal pain and who are seen by one of the study participants.  We will use the following exclusion criteria concerning patients with chest pain:   - Patients *younger than 18 years of age* will not be recruited because of limited ability to provide informed consent. - Patients with *limited ability to communicate in German* (the default language at the hospital) will not be recruited to exclude additional confounds related to language proficiency. - Patients with *dementia* will not be recruited to avoid additional confounds arising from pathological memory deficits. - Patients with *increased troponin level*, an indicator of myocardial infarction, will not be recruited to minimize stress on these more vulnerable patients. - Patients with none of five *cardiovascular risk factors* (cvRF; smoking history, diabetes, hypertension, dyslipidemia, age above 50 years, or family history of coronary heart disease) will not be recruited because chest pain symptoms in such patients are typically indicative of diagnoses unrelated to coronary heart disease, requiring a very different follow-up and health management recommendations (e.g., in the case of an anxiety disorder).   We will use the following exclusion criteria concerning patients with abdominal pain:   - Patients *younger than 18 years of age* will not be recruited because of limited ability to provide informed consent. - Patients with *limited ability to communicate in German* (the default language at the hospital) will not be recruited to exclude additional confounds related to language proficiency. - Patients with *dementia* will not be recruited to avoid additional confounds arising from pathological memory deficits. |
| **Measurements and Procedures:** | Study Procedure  The study involves two components: (a) the intervention component, consisting of the two physician-training programs and (b) the evaluation component, consisting of an assessment of the interventions through patient testing and interviews.  Physician Training  Physicians will be recruited to participate in the study, which will serve as a complement to physicians’ regular emergency department training. The two programs will follow the same structure, with physicians receiving the same intensity of teaching. Both programs will consist of one four-hour session of training with an experienced communication expert ([name] [name]). Also, both training programs will consist of theory and practice components as well as a test session to assess the actual use of communication skills. The information-structuring program will include a review of scientific evidence on the superiority of structured over non-structured communication as well as hands-on practical exercises in dyads to train structured communication skills. Specifically, participants will be introduced to the ‘InFARcT-scheme’ (categorization scheme that could, in principle, help physicians to structure information; for more information see: past work by research team) and trained to use it to structure their communication. The emotion skills training program will follow a similar structure but will focus on the NURSE communication model.^28^ The NURSE model encourages caretakers to engage in naming, understanding, respecting, supporting, and exploring patients’ emotional reactions with the goal of reducing anxiety and increasing compliance. In addition, physicians in both conditions will receive a one-hour booster session two weeks after the initial training involving a discussion of patient examples to whom they had applied the newly acquired skills. The rationale for the use of a booster session is to ensure that communication goals are maintained as a high priority and that physicians have a chance to receive additional feedback early in their training.  Patient Interviews  All physicians participating in the study will be asked to contact a member of the study team about any pending discharge communication with a patient suffering from chest pain or a patient suffering from abdominal pain. Eligible participants (see section on Participants) will be asked to give written consent to participate in the study and complete a pre-discharge assessment. The pre-discharge assessment will take about 15 minutes and aims to collect basic demographic measures concerning each patient as well as a number of other measures that will serve as covariates in the analysis, such as patients’ health status, memory ability, state anxiety, state depression, and medical knowledge. The rationale for including these measures is that they are potential moderators of participants’ recall of discharge information and thus should be included in the statistical analysis.  Immediately after the discharge communication event, patients will be interviewed for up to five minutes to assess recall of information provided during the discharge consultation and to assess patients’ satisfaction with the encounter.  Finally, two brief interviews of 5–10 minutes will be conducted over the phone seven days after discharge and 30 days after discharge to retest recall of discharge information, thus assessing the reliability of the main outcome measure and the time component of recall. In addition, patients will be asked about self-reported adherence to discharge recommendations, and overall assessment of the discharge consultation. Table 4 provides a description of the measures collected in each phase. Patients will also be asked about information provided by their General Practitioners to control for possible confounds of receiving extra or additional information from a third-party.  The discharge communication encounter as well as all interviews will be recorded with audio recording devices. |
| **Study Product/Intervention according to KlinV, if applicable:** | No medicaments are additionally being given to the patients. The intervention is the communication skills training for the physicians. |
| **Comparator(s) (if applicable):** | We will compare the effects of information structuring to a control training condition in which physicians will receive emotion skills training by the same experts. A systematic review of emotion skills training suggests that these have the potential to improve physician–patient interactions.^23^ However, emotion skills interventions are not geared to changing the structure of the information provided and thus represent a powerful control for our study. In particular, it will ensure that any effects in information recall and patient satisfaction can be attributed to the information structuring program rather than a general emphasis on communication training and patient satisfaction during physician training. |
| **Number of Participants with Rationale (if no Power Analysis conducted):** | Within three months 50 patients with chest pain and 50 patients with abdominal pain will be recruited. Including 4 groups with 100 patients each this sums up in 400 patients in one year. Sample of 400 gives acceptable power of .8 for comparison of two groups.  We based our sample sizes on calculations based on previous studies that compared an information structuring intervention relative to treatment as usual and suggest a medium effect size d = .59 for the intervention. To compute power for our planned analysis we conducted simulations in which we generated data using the means and standard deviations as those observed in the previous study but let patients be sampled from an homogenous pool of 6 physicians and varied the sample sizes per intervention group from 40 to 120. We then conducted 1000 repeated iterations for each sample size and analysed the data with a mixed effects model of patient’s recall clustered by physician and calculated the frequency of observing a significant effect of intervention for each sample size. A sample size of 100 participants per condition guarantees an appropriate power of over .9. Please note that while a smaller sample sizes per condition of over 50 would guarantee satisfactory power levels above .8, having a larger initial sample size is of importance given the possible attrition rates between the first measurement point (immediately after discharge) and the two planned follow-ups (over the telephone). Specifically, our desired sample size guarantees that we would have power above .9 for the analysis of the follow-up measurements in the face of 25% attrition rates over measurement occasions. |
| **Study Duration:** | The study will start at 02/01/2015 and will end at 31/12/2015 (=1 year). |
| **Study Schedule:** | First contact with study participants will be the 02/01/2015 when [name]. [name] will teach the first cohort of physicians. The last contact with participants will be the last doctor patient communication (approx. 31/12/2015). |
| **Investigator(s):** | [name]. [name]  Universitätsspital Basel  Interdisziplinäre Notfallstation  [name]  4031 Basel  Schweiz  PD [name]  Universitätsspital Basel  [name]  4031 Basel  Schweiz  [name]  Interdisziplinäre Notfallstation  [name]  4031 Basel  Schweiz |
| **Study Centre(s):** | Emergency Department  University Hospital of Basel  [name]  4031 Basel  Switzerland |
| **Statistical Analysis incl. Power Analysis** | The evaluation of the effects of the two training programs will be conducted using mixed-effects model.^33^ Mixed-effects models are statistical models containing both fixed (e.g., intervention program) and random (e.g., patient) effects and are used in a variety of disciplines including medical and social sciences, where repeated measurements are made on the same statistical units or on clusters of related statistical units. Specifically, our analysis will take into account the fact that physicians belong to particular clusters (see Study Design) and the same physician treats several patients, by clustering physicians by training program and patients by physician. These multivariate analysis methods also allow for simultaneous statistical adjustment for covariates of interest, including patient characteristics, such as age, memory ability, and so on. Similar models will be used to estimate the effect of the training programs on patient satisfaction, and adherence to discharge recommendations. |
| **GCP Statement:** | This study will be conducted in compliance with the protocol, the current version of the Declaration of Helsinki, the ICH-GCP or ISO EN 14155 (as far as applicable) as well as all national legal and regulatory requirements. |

study summary in local language

Allgemeine Informationen:

Wir führen eine Studie mit vierhundert Patienten durch, die zum Ziel hat, die Kommunikation zwischen Ärzten und Patienten, die mit Thoraxschmerzen oder Bauchschmerzen zu uns auf die Notfallstation kommen, zu verbessern.

Ziel der Studie:

Adäquate Informationsvermittlung beim Austritt eines Patienten nach einem Krankenhausaufenthalt kann einen grossen Einfluss auf die Lebensqualität des Patienten sowie auf andere Aspekte wie die Rehospitalisierungrate und die Gesundheitskosten haben. Die bisherige Forschung konzentrierte sich vor allem auf die Form/Art der Austritts-Informationsvermittlung (z.B. mündlich vs. schriftlich), der Darbietung solcher Informationen, insbesondere im Notfall-Setting, wurde bis anhin kaum erforscht. Unser Ziel ist es deshalb, die Darbietung der Austrittskommunikation (bei Patienten mit Thoraxschmerzen und bei Patienten mit Bauchschmerzen) zu ermitteln, welche, aus gesundheitspolitischer Sicht, zu verbesserten Outcomes führt.

Study schedule

We plan to conduct a cluster randomized controlled trial to test the effect of two physician training programs on patient information recall, namely, an information structuring training and an emotion skills training. Physicians that receive training at the University Hospital Basel usually stay for a six-month period in the emergency department before rotating to another department, with a new clusters of six physicians initiating training every three months. Consequently, the study will run for one year and involve four different clusters of physicians to ensure that sufficient physicians and associated patients can be included in the study (see also section on Participants below). Clusters of physicians will thus be pseudo-randomly assigned to one of the two training programs (information structuring vs. emotion-handling skills training). Patients attended by physicians from each respective cluster will be tested and interviewed to provide an assessment of the effects of the two training programs.

There will be a pre-discharge assessment, an interview immediately after the discharge event and a telephone interview one week and 30 days after the discharge event.

Training/Interviewing Timeline for Each Cluster of Physicians (*k*)/Patients (*n*)

| Cluster | Months 1-3 | Months 4-6 | Months 7-9 | Months 10-12 |
| --- | --- | --- | --- | --- |
| 1 | Information Structuring  (*k*=6, *n* = 100) |  |  |  |
| 2 |  | Emotion Skills  (*k*=6, *n* = 100) |  |  |
| 3 |  |  | Information Structuring  (*k*=6, *n* = 100) |  |
| 4 |  |  |  | Emotion Skills  (*k*=6, *n* = 100) |

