Our analyses had two aims. First, our main goal was to test the effects of information structuring on information recall and possible interactions with prior expertise. Second, we tested for superiority of information structuring relative to unstructured communication on perceived comprehensibleness and satisfaction. In total, participants recalled 9 of 28 items presented by the emergency physician (range: 0-23 items). An analysis of variance with condition (structured vs. unstructured), group (third-year medical, first-year medical, first-year psychology), and their interaction as factors, revealed a main effect of structure, *F*(1,228)=26.6, *p* < .001, as well as a expertise, F(2,228)=7.0, *p* = .009. As can be seen in Figure 2B, those participants that viewed the video structured according to the InFARCt categories listed 1 to 3 additional pieces of information relative to those who viewed the unstructured video. Also, third-year medical students did considerably better than first-year medical students, who, in turn, outperformed psychology students. Although the condition by expertise interaction was not significant, *F*(2,228)=0.8, *p* = .44, the magnitude of the effects of information structuring seem to vary systematically by expertise: Although only a negligible difference of structured information could be observed in the expert group (13.5 [SD = 4.5] vs. 13.0 [SD = 4.6], Cohen’s *d* = .11), we found a small effect size of information structuring in first-year medical students (9.9 [SD = 5.1] vs. 8.8 [SD = 4.5], Cohen’s *d* = .23), and a medium effect size in first-year psychology students (8.1 [SD = 4.3] vs. 5.7 [SD = 3.7], Cohen’s *d* = .60). In addition, as can be seen in Figure 2C, participants that viewed the InFARCt video provided higher ratings on items assessing comprehensibleness, structure, and willingness to recommend the physician to family and friends.

Overall, these results suggest that participants without expert medical knowledge (i.e., psychology students) can profit from information structuring during discharge communication events. The results are encouraging in suggesting that an intervention aimed at introducing information structuring in physicians’ communication can lead to improved recall of discharge information, perceived understanding, and increased satisfaction with the communication event.

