## Determination of Sample Size

Within three months 50 patients with chest pain and 50 patients with abdominal pain will be recruited. Including 4 groups with 100 patients this sums up in 400 patients in one year. Sample of 400 gives acceptable power of .8 for comparison of four groups for medium effect sizes of .4.

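### The two sample-size statements contradict each other, and their power figures take no account of allocation by four cohorts, two per training program

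*Protocol*

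**What the plan says.** The synopsis (Number of Participants with Rationale) makes two power claims. It first says: "Sample of 400 gives acceptable power of .8 for comparison of two groups", with no effect size attached. It then cites previous studies of information structuring against usual treatment, which "suggest a medium effect size d = .59 for the intervention". The simulation built on that effect "let patients be sampled from an homogenous pool of 6 physicians and varied the sample sizes per intervention group from 40 to 120", and the simulated data were analysed by a mixed model clustered by physician. The reported results are that "A sample size of 100 participants per condition guarantees an appropriate power of over .9" and that "smaller sample sizes per condition of over 50 would guarantee satisfactory power levels above .8". Power above .9 is also claimed for the follow-up measurements with 25% attrition. No ICC, between-physician variance, cohort variance or significance level is given.

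Section 11.2 says: "Sample of 400 gives acceptable power of .8 for comparison of four groups for medium effect sizes of .4".

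The design (sections 6.1 and 6.2.1, Table 3) has four consecutive three-month cohorts of six physicians and 100 patients. Two cohorts go to each training program, which makes 12 physicians and 200 patients per program. Section 7.3 randomises the first cohort's training and alternates thereafter. Section 11.4 plans a mixed model that is to reflect cluster membership, but it then describes patients nested in physicians and physicians nested in training program, without an explicit cohort term.

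**The concern.** The two sections give different numbers of groups for the same 400 patients, and only one of them names an effect size beside its .8. Within the synopsis, .8 with 400 patients stands next to over .9 with 100 per condition, which cannot both describe one effect and one test. The simulated layout (100 patients per condition, a pool of six physicians) is not the trial's layout. The variance that matters most when training is allocated to whole cohorts, namely variation between cohorts, does not appear at all.

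At stake is what the trial can claim about its own sensitivity. A power described as guaranteed, when the calculation leaves out the allocated unit, gives readers a poor basis for judging a null result.

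**Working it through.** **Inputs.** From the synopsis: d = .59; 50 and 100 patients per condition; 25% attrition (75 left of 100). From section 11.2: effect .4 and N = 400. From Table 3: per program, 2 cohorts, 12 physicians and 200 patients, so m = 100/6 = 16.7 patients per physician. Assumed, because the protocol gives none: two-sided alpha .05, physician ICC (ρp) .02 to .10, cohort ICC (ρc) 0 to .01. Outcome SD is set to 1.

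**1. The synopsis figures.** Unclustered two-sample t-test, non-centrality d·√(n/2), 2n − 2 df, d = .59:
- n = 50: .59 × √25 = 2.95, power 0.83
- n = 75: 3.61, power 0.95
- n = 100: 4.17, power 0.99

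The claims of above .8, above .9 after attrition, and over .9 all reproduce with independent patients.

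**2. The .8 statements.** Same test at d = .4:
- 100 v 100: .4 × √50 = 2.83, power 0.80
- 200 v 200: .4 × √100 = 4.00, power 0.98

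A four-group ANOVA on 400 does not give .8 under the readings tried. It gives above 0.999 if .4 is Cohen's f. If .4 is the largest pairwise d, it gives 0.65 (f = .4/√8 = .141) to 0.93 (f = .2), depending on the pattern of means. So 0.80 at .4 is the power to compare two single cohorts of 100, which is not the trial's comparison.

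**3. Actual layout, physician clustering only.** Design effect DE = 1 + (16.7 − 1)ρp; SE = √(2·DE/200); 2 × (12 − 1) = 22 df.

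| ρp | DE | SE | Power, d = .59 | Power, d = .4 |
|---|---|---|---|---|
| .02 | 1.31 | 0.115 | 0.998 | 0.915 |
| .05 | 1.78 | 0.134 | 0.988 | 0.817 |
| .10 | 2.57 | 0.160 | 0.940 | 0.665 |

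**4. Actual layout, tested at the allocated unit.** Variance of a cohort mean v = ρc + ρp/6 + (1 − ρc − ρp)/100. With two cohorts per program, SE = √(2v/2) = √v, on 4 − 2 = 2 df (critical t = 4.30).

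| ρp | ρc | v | SE | Power, d = .59 | Power, d = .4 |
|---|---|---|---|---|---|
| 0 | 0 | .0100 | 0.100 | 0.826 | 0.565 |
| .05 | 0 | .0178 | 0.134 | 0.633 | 0.387 |
| .05 | .01 | .0277 | 0.167 | 0.485 | 0.283 |

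The first row needs no ICC assumption: the loss comes entirely from having 2 df.

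**5. Source of the effect.** The synopsis credits d = .59 to earlier studies against usual treatment. Section 3.1 (State of Research) says that structuring had not yet been studied for delivering discharge information. The recall data the protocol does report are from Study 4, a student video experiment, with d of .11, .23 and .60 in three groups. The origin of .59 is therefore not traceable in the document.

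**The case against.** The best defence is that the trial recruits twice the patients and physicians per condition that were simulated, and that the planned model clusters by physician. On that basis over .9 at d = .59 survives every physician ICC tried up to .10, and .8 at an effect of .4 survives to about ICC .05 (0.817). This stands. A reader might infer that ignoring differences between physicians by itself destroys the stated power. It would on the simulated layout: 100 patients and six physicians per condition give 0.80 at ICC .05 and 0.65 at ICC .10. That is not the layout of this trial.

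The defence also says that a 2-df test is one choice of analysis. That is fair, but the 22-df figures hold only if cohorts do not differ. With ρp = .05 and ρc = .01, a test that omits cohort understates the SE by a factor √(.0177/.0277) = 0.80. Its type I error is then about 0.12 instead of .05 (normal approximation). Section 11.4 itself undertakes to reflect cluster membership, so the power statement must say which level is tested.

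Three further inferences are tempting but not supported:
- **That .59 was picked as the most favourable subgroup.** It is close to the psychology students' .60, but the protocol does not say so. Those students were the lay group, and section 3.1 argues beforehand that structure should help such people most.
- **That Study 4's true overall effect is about .35.** This requires replacing the printed F for structure and assuming equal arms.
- **That the printed F = 26.6 is impossible.** The printed p = .009 does fit F(1,228) = 7.0 (p = 0.0087) and not "as well as a expertise, F(2,228)=7.0" (p = 0.0011), so a transposition is likely. The group sizes are not given, however, and strongly unbalanced cells could change the picture. It is a minor background correction and does not alter the sample-size text.

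**Conclusion.** The point holds as an inconsistency and an omission. The synopsis arithmetic is correct for independent patients. The contradiction between the synopsis and section 11.2 needs no assumption beyond the text. That 0.80 at .4 reproduces only for 100 v 100, and that a cohort-level test gives at most 0.826 at d = .59 and 0.565 at .4, requires only a two-sided .05 level. Figures below those ceilings depend on assumed ICCs and illustrate a range.

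The shortfall at d = .59 comes from allocating four cohorts, not from physician heterogeneity. At .4, power can fall below .8 on either level of testing. The power statements should be corrected because they contradict each other and are not met at the unit the trial allocates.

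**What to change.** Replace the synopsis text and section 11.2 with one statement:
- Two conditions, each with 200 patients, 12 physicians and 2 cohorts.
- Power computed with the same test as the primary analysis, at a stated alpha, over stated ranges of physician and cohort ICC.
- The claim of guaranteed power and the reference to four groups removed.
- A plain sentence on the limit set by four cohorts, including the 2-df ceiling if cohort is the level of inference.
- The source of d = .59, with power also shown at a smaller effect, such as the .4 already in section 11.2.

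Separately, check the two F values in Study 4 and correct them if transposed.

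The cost is a short simulation and two rewritten paragraphs. No patients are added and the design does not change. The stated power will look less favourable wherever cohort-level inference is shown.
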